#### Secondary Outcomes are Categorised for the Neonate and the Mother as Follows

Neonatal: Gestational age at delivery, preterm delivery (<37 weeks), large/small-for-gestational age (using local, national, and international centiles and customised centiles), amniotic fluid glucose, cord blood C-peptide, admission to the neonatal intensive care unit (NICU), duration of admission to NICU, neonatal jaundice requiring phototherapy, Apgar scores, body composition and anthropometry, neonatal hypoglycaemia (defined as a capillary glucose <2.6 mmol/L on one or more occasions, within the first 48 h of life starting at least 30 min after birth, and necessitating treatment either with 40% glucose gel administered to the buccal mucosa and/or with intravenous dextrose), neonatal nasogastric feeding, and feeding type on discharge from hospital. Infant feeding choices and feeding history will also be examined at six weeks postpartum. Neonatal anthropometry; for each of the four skinfold thickness measurements, an internal standard deviation score (SDS) will be calculated, using residuals from a linear regression model, adjusting for infancy age, gestational age at birth, and sex. Mean skinfold thickness SDS will be used in analyses. Birth ponderal index will be calculated by dividing the infant’s birthweight by its birth length cubed (kg/m^3^). Secondary analysis for sex-appropriate SDS scores will also be assessed using different growth centiles such as GROW centiles [33] and INTERGROWTH centiles [34].

Maternal outcomes at 32 weeks, 36 weeks and postpartum: Maternal outcomes to be studied include maternal weight, BMI, glycaemia (CGM metrics as per the international consensus recommendations [35], HbA1c), cardiometabolic health (blood pressure, lipids, fasting insulin, fasting glucose), maternal food choice and eating behaviour, quality of life, treatments administered for GDM, birth modality and complications, and postpartum glycaemia (measured by two-point OGTT and CGM).

### 2.9. Sample Size Justification

Retrospective data assessing the effect of late gestational weight gain (GWG) upon pregnancy outcomes were used to inform the sample size calculation [36]. The following sample size examples are based upon alpha 0.05 and power 0.9.

In the retrospective study, women had a standard deviation of 2 kg for late GWG and <3 kg for total GWG. Allowing for a standard deviation of 3 kg and a 1 kg difference between groups, 190 women per group will be required to give 90% power for the primary maternal endpoint.

The neonatal primary endpoint will be standardised birthweight. Recruitment of 175 women per group will give 90% power for identification of a 0.3 sd difference in standardised birthweight. As the standard deviation for birthweight was 508 g, this broadly equates to a difference in birthweight of 150 g.

A study size of 500 participants will provide sufficient statistical power and will allow for a 20–25% withdrawal rate. This sample size will also give sufficient power to detect secondary outcomes:To identify an increase in LGA (odds ratio (OR) 2.25 at 80% power).To identify a difference in maternal glycaemia at 36 weeks, for example, differences in mean CGM glucose (0.3 mmol/L difference), time in target (8% difference in time in target (3.5–7.8 mmol/L; >100 min per day), which has been associated with clinically relevant differences in neonatal outcomes) [8].To identify a 0.7 mmol/L difference in maternal postnatal two-hour OGTT glucose.

Several secondary analyses will be performed. A per protocol analysis will be performed in participants with >80% compliance and at least four weeks’ exposure to the intervention. Data will be used in a qualitative way to assess predictors for withdrawal or poor compliance. Consent will also be taken to collect and analyse outcomes for women who withdraw from the study, to allow assessment of reasons for withdrawal and their bearing upon outcomes.

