### 2.10. Statistical Analysis

An intention to treat analysis of the co-primary outcomes will be based on t-tests between trial arms and linear regression models with adjustment for baseline variables and the stratification variable of study centre using a fixed effects model. In addition, the model for maternal gestational weight change will be adjusted for baseline weight as an explanatory variable. The potential role of other explanatory variables such as pre-pregnancy BMI or information from the questionnaires will be investigated in sensitivity analyses. Secondary outcomes will be examined through regression analyses (linear or logistic) appropriate for the type of outcome being considered. A further secondary analysis will be performed to assess if main results are altered with addition of early GWG to the regression model. Safety analyses will be performed to assess any quantitative difference in effects, rates of small-for-gestational-age (SGA)/IUGR, stillbirth, neonatal hypoglycaemia, and admission to NICU.

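### Neonatal co-primary endpoint: 175 women per group give 80%, not 90%, power for a 0.3 SD birthweight difference; 90% needs about 234 per group with birthweight

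*Protocol article*

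**What the plan says.** Section 2.8 of the protocol article names two co-primary endpoints: maternal weight change to 36 weeks and neonatal birthweight. Section 2.9 opens its calculations with common settings: "The following sample size examples are based upon alpha 0.05 and power 0.9".

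- **Maternal endpoint.** For a 1 kg difference and an SD of 3 kg, it concludes that "190 women per group will be required to give 90% power for the primary maternal endpoint".
- **Neonatal endpoint.** "Recruitment of 175 women per group will give 90% power for identification of a 0.3 sd difference in standardised birthweight". With a birthweight SD of 508 g, the section converts this to roughly 150 g.
- **Total.** "A study size of 500 participants will provide sufficient statistical power and will allow for a 20–25% withdrawal rate".
- **Women who withdraw.** "Consent will also be taken to collect and analyse outcomes for women who withdraw from the study".

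Section 2.10 gives the analysis: "An intention to treat analysis of the co-primary outcomes will be based on t-tests between trial arms and linear regression models". The regressions also adjust for centre and for baseline covariates.

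**The concern.** The two co-primary calculations share one alpha and one power but come out in the wrong order. The neonatal effect (0.3 SD) is smaller than the maternal one (1 kg / 3 kg = 0.333 SD), so it must need more women than the maternal 190 per group. The protocol says it needs fewer.

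Two things are at stake. As written, the maternal endpoint appears to be the more demanding one, when at the stated inputs it is the neonatal endpoint. And a null birthweight result would be read against a 90% power for 0.3 SD that 175 women per group do not supply, and that 500 randomised women supply only if few birthweights are missing.

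**Working it through.** **Inputs.** All are from section 2.9, except the test, which is from section 2.10.

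- Alpha 0.05. Sidedness is not stated; two-sided is taken first and one-sided is tried below.
- Target power 0.90.
- Neonatal: difference 0.3 SD, 175 per group. Birthweight SD 508 g.
- Maternal: difference 1 kg, SD 3 kg, 190 per group.
- 500 randomised, 250 per group if equally allocated; allowance 20–25%.
- Two-sample t-test.

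**Formulas.** With standardised difference d: n per group = 2(z₁₋α/₂ + z_power)² / d², and power = Φ(d√(n/2) − z₁₋α/₂).

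**Step 1. The stated neonatal figure.** At n = 175 and d = 0.3: 0.3 × √87.5 = 2.806; 2.806 − 1.960 = 0.846; power = 80.1% (exact t: 79.9%). The stated 90% is not reproduced.

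- n for 90%: 2(1.960 + 1.2816)² / 0.09 = 233.5, so 234 per group (exact t: 234.5).
- n for 80%: 2(1.960 + 0.8416)² / 0.09 = 174.4, so 175 per group.

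The stated 175 is therefore the 80% answer.

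**Step 2. The maternal figure as a check on the method.** 2(1.960 + 1.2816)² × 3² / 1² = 189.1, so 190 per group. This reproduces the protocol's number with two-sided 0.05. One-sided would give 2(1.645 + 1.2816)² × 9 = 154.2, so 155.

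Scaling the maternal result to the neonatal effect gives the same answer as step 1: 189.1 × (0.3333 / 0.3)² = 233.5.

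**Step 3. Other readings of the neonatal sentence.**

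- One-sided 0.05: power at 175 is 87.7% (exact t 87.6%); 90% needs 191 per group.
- The gram conversion, 150 / 508 = 0.295 SD: power 78.9%; 90% needs 242 per group.
- Alpha split to 0.025 for two endpoints: power 71.4%.
- Covariate adjustment: 90% at 175 needs a correlation of √(1 − 175/233.5) ≈ 0.50 between covariates and standardised birthweight. Section 2.9 assumes none.

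None of these reaches 90% on what the section states.

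**Step 4. What 500 randomised women deliver for 0.3 SD** (two-sided 0.05, equal groups, unadjusted, normal approximation):

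| Birthweight missing | Women with birthweight | Per group | d√(n/2) | Power |
|---|---|---|---|---|
| 0% | 500 | 250 | 3.354 | 91.8% |
| 6.4% | 468 | 234 | 3.245 | 90% |
| 10% | 450 | 225 | 3.182 | 89% |
| 20% | 400 | 200 | 3.000 | 85.1% |
| 25% | 375 | 187.5 | 2.905 | 82.8% |

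Exact t gives 91.7% at 250, 84.9% at 200 and 82.6% at 187.5 per group. The 6.4% is 1 − 468/500.

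**Step 5. Difference detectable with 90% power at 20–25% loss.** By exact t, 0.325 SD at 200 per group and 0.336 SD at 187.5 per group. In grams: 0.325 × 508 = 165 and 0.336 × 508 = 171.

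**The case against.** **The 83–85% is a lower bound, not the trial's power.** This stands. It requires that no woman who withdraws has a birthweight. The protocol plans consent to collect outcomes after withdrawal and an intention-to-treat analysis, so birthweight may well be available for many of them. On the other side, that consent is described as serving to study reasons for withdrawal and their bearing on outcomes. The article does not say that these women enter the primary analysis, so the upper figure cannot simply be credited either.

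**Regression adjustment may recover power.** With 200 or 187.5 per group, covariates explaining about 14% (1 − 200/233.5) or 20% (1 − 187.5/233.5) of the variance would restore 90%. Section 2.9 neither gives nor uses such a figure. This is a caveat on step 4 and does not make the 175 sentence true.

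**A reader might infer that the 500 and its withdrawal allowance were built on the erroneous 175.** The figures point the other way. The maternal requirement leaves (500 − 380) / 500 = 24%, inside the stated 20–25%. The 175 figure would leave (500 − 350) / 500 = 30%, outside it. The enrolment target fits the maternal calculation, which is correct.

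**A reader might also infer a 20% type II error for the trial.** That describes 175 per group. The plan is 250 per group, and even a 25% loss leaves 187.5.

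**Conclusion.** The stated neonatal power is wrong as written: 80% rather than 90% at 175 per group, with about 234 per group needed for 90%. This follows from the section's own inputs and its own maternal calculation, and no reading that the article states or uses rescues it. An article's condensation does not explain it, because n, effect, alpha and power are all given.

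For the trial as planned the consequence is smaller and conditional. Power for 0.3 SD lies between about 83% and 92%, depending on birthweight capture, and 90% holds only with birthweight missing for no more than about 6% of randomised women. These figures assume two-sided 0.05, equal groups and no gain from covariates.

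It would go too far to conclude that the trial is too small or that the withdrawal margin does not exist for this endpoint. What matters is missing birthweight, not stopping the diet, and the documents do not say how many birthweights will be missing.

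**What to change.** In section 2.9, make two corrections.

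1. Correct the neonatal sentence: 175 per group gives 80% power for 0.3 SD at two-sided 0.05; alternatively, about 234 per group are needed for 90%.
2. State what 500 randomised women give for the neonatal endpoint: about 92% power for 0.3 SD with birthweight for all, about 89% with 10% missing, and 83–85% with 20–25% missing (90% power then only for about 0.325–0.336 SD, 165–171 g). Add that 90% power for 0.3 SD requires birthweight to be missing for no more than about 6% of randomised women. Tie that condition to missing birthweight, not to withdrawal from the diet.

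The cost is a wording change and a less favourable stated power. Enrolment, conduct and analysis stay as they are.

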### 2.10. Statistical Analysis

An intention to treat analysis of the co-primary outcomes will be based on t-tests between trial arms and linear regression models with adjustment for baseline variables and the stratification variable of study centre using a fixed effects model. In addition, the model for maternal gestational weight change will be adjusted for baseline weight as an explanatory variable. The potential role of other explanatory variables such as pre-pregnancy BMI or information from the questionnaires will be investigated in sensitivity analyses. Secondary outcomes will be examined through regression analyses (linear or logistic) appropriate for the type of outcome being considered. A further secondary analysis will be performed to assess if main results are altered with addition of early GWG to the regression model. Safety analyses will be performed to assess any quantitative difference in effects, rates of small-for-gestational-age (SGA)/IUGR, stillbirth, neonatal hypoglycaemia, and admission to NICU.

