Interventions to change the overall energy intake of the diet in free-living conditions are challenging, with many studies having design limitations that reduce the validity of the results (reviewed in [40]). For example, randomisation and blinding in free-living trials is challenging and often not performed. Nutritional studies may be entirely self-reported and portion sizes cannot be controlled [41,42]. The diet boxes may support participants in following the prescribed diet by providing all the meals and snacks in an easy to follow format. The portions are controlled and all the nutrition required for a safe and healthy diet during pregnancy is provided.

Controlling gestational weight gain after 28 weeks may only give a relatively short time for intervening, but previous work has suggested that this still could have beneficial effects upon pregnancy outcomes [21]. Although there are no long term data about dietary interventions after 28 weeks, overall, gestational weight gain has an impact upon women’s weight for up to 15 years after the pregnancy [16]. There are several studies that support the potential benefits of controlling gestational weight gain after a diagnosis of GDM, and that address the issues of safety and timescales. We recently completed a retrospective study of 547 women with GDM [36]. Overall total gestational weight gain (0–36 weeks) was associated with increased rates of LGA, caesarean section, and reduced rates of vaginal deliveries. Late GWG was also associated with postpartum glucose homeostasis with a positive association with two-hour OGTT glucose concentration on the postpartum OGTT, raising the possibility that controlling GWG for a short 8–10 week period could lead to longer-term beneficial effects upon glucose tolerance and diabetes incidence [36].

DiGest is a randomised controlled blinded trial assessing whether an energy restricted diet in pregnant women with GDM can improve pregnancy outcomes for mother and child. Although the current evidence base suggests that controlling pregnancy-related weight gain can improve health outcomes, much of the traditional advice given to women in pregnancy today with growing rates of overweight and obesity is inappropriate. The common myth of ‘eating for two’ may be particularly detrimental for women with GDM.

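### Pre-pregnancy BMI and early weight gain, both known at baseline, are kept out of the primary models, which costs some precision, mainly for birthweight, but causes no bias

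*Protocol article*

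**What the plan says.** Section 2.10 (Statistical Analysis) bases both co-primary comparisons on t-tests and on linear regressions adjusted for baseline variables, which it does not list, and for study centre. It then places the maternal size variables as follows.

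- **Enrolment weight:** for the maternal outcome, "the model for maternal gestational weight change will be adjusted for baseline weight as an explanatory variable". No such statement is made for birthweight.
- **Pre-pregnancy BMI:** "The potential role of other explanatory variables such as pre-pregnancy BMI or information from the questionnaires will be investigated in sensitivity analyses".
- **Early gestational weight gain (GWG):** "A further secondary analysis will be performed to assess if main results are altered with addition of early GWG to the regression model".

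All the ingredients exist at baseline. BMI from measured booking weight is an eligibility criterion (section 2.2). Booking weight also serves as the pre-pregnancy weight in the exclusion for weight loss (section 2.3). Weight and height are measured at recruitment (section 2.5.1). Early gain is therefore a subtraction and needs no new data.

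The Discussion reports from the retrospective cohort that "Overall total gestational weight gain (0–36 weeks) was associated with increased rates of LGA". Section 2.8 describes the birthweight score as standardised for sex and gestational age, so the score itself does not absorb maternal weight or weight gain.

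**The concern.** In a randomised trial with a continuous outcome, a baseline variable that predicts the outcome belongs in the primary model, because it removes outcome variance at almost no cost. Here the candidate variables are already collected, and the protocol regards weight gain as related to infant size. They are nonetheless assigned to analyses that only check the main result.

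What is at stake is precision. It matters more for birthweight, whose power is below the planned 90%, than for maternal weight. The maternal model has a further weakness. Enrolment weight is booking weight plus early gain, and a single coefficient for the sum cannot let the two parts act differently on later gain.

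**Working it through.** **Inputs from section 2.9.** "The following sample size examples are based upon alpha 0.05 and power 0.9". I take alpha as two-sided and allocation as 1:1. Maternal endpoint: "Allowing for a standard deviation of 3 kg and a 1 kg difference between groups, 190 women per group will be required". Neonatal endpoint: "Recruitment of 175 women per group will give 90% power for identification of a 0.3 sd difference in standardised birthweight". Total size is 500 with 20–25% withdrawal, so 250 × 0.75 = 187.5 to 250 × 0.80 = 200 women per arm.

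**The plan's own figures.** n per group = 2(1.960 + 1.282)²(SD/difference)².

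- Maternal: 2 × 10.51 × (3/1)² = 189.1, so 190. This reproduces.
- Birthweight: 2 × 10.51 × (1/0.3)² = 233.5, so 234. The stated 175 gives 80% power, not 90%. That is a separate defect of section 2.9, and it matters here only because it leaves birthweight with no power to spare.

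**Gain for birthweight.** Adjustment shrinks the residual SD to √(1 − R²), so the required n is 233.5 × (1 − R²). Here R² is the extra variance explained by BMI (or booking weight) and early gain. The document gives no value, so it is varied.

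| Assumed extra R² | n per group for 90% | Power at 187.5 per arm | Power at 200 per arm |
|---|---|---|---|
| 0 | 234 | 82.8% | 85.1% |
| 0.02 | 229 | 83.5% | 85.8% |
| 0.05 | 222 | 84.6% | 86.8% |
| 0.10 | 211 | 86.5% | 88.5% |
| 0.20 | 187 | 90.1% | 91.8% |

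Reaching 90% would need R² = 1 − 200/233.5 = 0.14 to 1 − 187.5/233.5 = 0.20.

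**How variable early gain is.** Section 2.9 reports that "women had a standard deviation of 2 kg for late GWG and <3 kg for total GWG". If total gain is early plus late gain, with early/late correlation r, then s² + 2² + 2·r·2·s < 3², so s < −2r + √(4r² + 5).

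- r = +0.3: s < 1.7 kg
- r = 0: s < 2.2 kg
- r = −0.3: s < 2.9 kg

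**What enrolment weight captures in the maternal model.** The booking-weight SD and the correlations below are assumptions. With booking weight and early gain uncorrelated, the correlation of enrolment weight with later gain is (r_b·s_b + r_e·s_e)/√(s_b² + s_e²).

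- Booking-weight SD 15 kg, early-gain SD 1.7 kg, correlations −0.25 and +0.3: (−3.75 + 0.51)/15.10 = −0.215. Enrolment weight explains 4.6% of the variance and booking weight alone 6.25%. The two terms entered separately explain 0.0625 + 0.09 = 15.25%.
- Booking-weight SD 20 kg, early-gain SD 1.7 kg, correlations −0.2 and +0.3: 3.0% for enrolment weight against 13.0% for both terms. The required n falls from 184 to 165 per group, and power at 187.5 per arm rises from 90.6% to 93.3%.

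In both examples enrolment weight correlates 0.99 or more with booking weight. Across booking-weight SD 15–20 kg, early-gain SD 1.7–2.9 kg and correlations of −0.15 to −0.25 and +0.2 to +0.3, enrolment weight explains about 1–5% and the two terms about 6–15%.

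**The case against.** The strongest reply is that nothing here is an error. Omitting a prognostic covariate from a linear model neither biases the randomised comparison nor inflates the type I error. Both variables are pre-specified for supporting analyses, so readers will see whether they change the result. The birthweight gain is a few points of power. The maternal endpoint needs little help: its SD of 3 kg is cautious, and at the retrospective late-gain SD of 2 kg, 190 per group gives over 99% power for 1 kg. All of this stands, and it limits the point to an improvement in precision.

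Several stronger readings are tempting but not supported.

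- *The birthweight model contains no maternal size variable.* The wording suggests it, since baseline weight is added only for the mother and BMI is listed among other variables. But the baseline variables are unnamed, and an analysis plan not shown may list them.
- *The two parts of enrolment weight cancel.* Appreciable cancelling needs an early-gain SD of around 5 kg. In the first example that would lower the 4.6% to 2.0%. But with late-gain SD 2 kg and r = +0.3 it implies a total-gain SD of √(25 + 4 + 6) = 5.9 kg, about twice the ceiling in section 2.9. Early gain is swamped by booking weight rather than cancelled.
- *The document ties BMI to infant size.* It links weight gain to infant size, but not BMI. The cohort finding also concerns gain over the whole period to 36 weeks, not early gain alone.
- *The plan will adjust for eating behaviour measured after randomisation.* Questionnaires are repeated at later visits and the sentence sets no visit limit. But it concerns sensitivity analyses only, and nothing says that later values will be used.

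One practical objection also stands. Diagnosis ranges from 20 to 30 + 6 weeks, so enrolment minus booking weight partly reflects when a woman enrolled. The fix must allow for that.

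**Conclusion.** The point holds as a matter of precision. Section 2.10 assigns BMI and early gain to supporting analyses although both are available at baseline. For birthweight, including them would raise power from about 83–85% to about 84–89% if they explain an extra 2–10% of the variance. Restoring the planned 90% would take 14–20%, so adjustment alone should not be counted on to repair the sample size. For maternal weight the benefit is about 3 points in the worked example, on an endpoint already at about 90–92% (R² = 0).

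These figures rest on two-sided alpha, equal allocation, withdrawn women contributing no outcome, and assumed R² values, correlations and booking-weight SD. Section 2.9 plans to collect outcomes after withdrawal with consent, which would raise all the power figures. The bound on early-gain SD assumes that the retrospective cohort resembles the trial and that total gain is the sum of early and late gain.

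**What to change.** In section 2.10, name the baseline variables. In the primary regression of both co-primaries, pre-specify these separate terms:

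- booking weight (or pre-pregnancy BMI);
- early gain, defined as enrolment weight minus booking weight;
- gestational age at enrolment, because enrolment timing varies;
- study centre.

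In the maternal model, the booking-weight and early-gain terms replace enrolment weight alone. Keep the model without them as the sensitivity analysis. Where questionnaire covariates are used in sensitivity analyses, state that they take their visit 1 values.

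The cost is a minor change of wording and a few degrees of freedom. No new data are needed. The change should be made before any comparison by arm is seen.
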